### Concealment mechanism {16b}

The randomization list will be sent to the drug packaging manager, then the masked list will be entered into the eCRF system by an information technology manager.

### Implementation {16c}

The randomization list will remain the responsibility of the independent Statistician throughout the duration of the trial. The Statistician will provide envelopes containing individual patient randomization codes to the Investigator, which will remain closed even after the database has been locked.

## Assignment of interventions: Blinding

### Who will be blinded {17a}

Treatment group allocation will remain unknown to patients, investigators, and researchers (i.e., laboratory analysis, data collection, and statistical analysis).

### Procedure for unblinding if needed {17b}

Unblinding of an individual randomization code is permitted in the event of a serious AE (SAE) if it is considered useful for the patient’s safety. Only the Investigator is permitted to open the envelope and the code breach will be clearly indicated in the eCRF and in the envelope itself, which will be re-sealed. The Investigator will inform the trial Monitor immediately that the code has been opened.

## Data collection and management

### Plans for assessment and collection of outcomes {18a}

The CRO, Clinical Trial Consulting, will create and manage the e-CRFs on behalf of the study Sponsor. The Sponsor will then provide this set-format e-CRF to investigators to record the required trial data at each visit (day 0–day 70), with internal controls to help ensure correct data entry. Trial data for each participant will be entered into the e-CRF by the Investigator and collated by the study centers. All safety data (AEs, physical examinations, vital sign measurements and laboratory assessments) will be recorded in patients’ medical records and in the e-CRF. Data cleaning analysis conducted by the Data Manager (an employee of CMV-Stat, Rome, Italy) will identify any inconsistencies to the Investigator for validation (i.e., modification or acceptance).

At the end of the trial, the database will be frozen by the Data Manager and the data sent to the biostatistics unit of CMV-Stat for statistical analysis. All methods used for statistical analyses of data will be listed in detail in the statistical analysis plan (SAP), which will be finalized in Version 1.0 of the SAP, prior to the database lock.

### Plans to promote participant retention and complete follow-up {18b}

Patients will be offered the option to be visited by a clinician from the participating centers at any time, if needed or requested by a patient.

### Data management {19}

Data management and control procedures will be documented in the monitoring plan prior to trial initiation. At the end of the trial, all sets of envelopes will be archived in the trial master file. All essential trial documents will be conserved by the trial centers for ≥ 25 years in accordance with GCP and applicable regulatory requirements.

### Confidentiality {27}

Confidentiality of data will be maintained by the use of coding only to identify patients. Neither the Sponsor nor collaborators may lawfully use patients’ personal data without first obtaining appropriate and specific expressions of consent.

### Plans for collection, laboratory evaluation, and storage of biological specimens for genetic or molecular analysis in this trial/future use {33}

Data and biological samples may be used in future trial and research activities if specific consent to do so has been provided by the individual patients during the written informed consent process. In the event that a patient withdraws from the trial, all stored biological samples permitting patient identification will be destroyed.

## Statistical methods

### Statistical methods for primary and secondary outcomes {20a}

The statistical analysis of data from the trial will be conducted by a statistician from CMV-Stat on behalf of the Sponsor.

All the variables will be analyzed descriptively using means with SDs, medians with interquartile ranges (IQRs), minimum and maximum values, and 95% confidence intervals (where appropriate) for continuous variables, and numbers, percentages, and missing data for categorial variables.

For all trial endpoints, analyses will be performed on each timepoint in absolute terms and as changes from baseline. Efficacy endpoints will be analyzed according to the stratification factor of the presence of uncomplicated HD versus thrombosed hemorrhoids. Efficacy analysis will be applied in the intention-to-treat (ITT) and per protocol (PP) populations and safety/tolerability will be assessed in the safety population. The ITT population is defined as all patients who have taken ≥ 1 dose of study drug/placebo and who have ≥ 1 post-baseline assessment for the primary endpoint. The PP population is defined as all enrolled patients who have data from all observations, met all inclusion/exclusion criteria, not taken any unauthorized drug, and taken ≥ 80% of the study drug/placebo. The safety population is defined as all patients who have signed informed consent and have taken ≥ 1 dose of study drug/placebo.

For the primary endpoint (i.e., change in HDSS from baseline to day 40 in the ITT population), the *t*-test will be applied with a significance level of 5%. If assumptions of normality and homoscedasticity are unmet, a corresponding non-parametric test will be applied.

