### Sample size {14}

The trial aims to enroll a total of 50 patients (25 patients in each treatment group). This sample size is based on an assumed between-group difference in HDSS score of 1.8 points with a standard deviation (SD) of 1.7 (based on results of previous studies [31, 32]), an alpha of 0.05, and a two-tailed *t*-test with 90% power to reject the null hypothesis (i.e., the averages of the two treatment groups are equal) and an expected drop-out rate of approximately 10%.

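### The primary test is switched on the observed outcome data, and the non-parametric fallback, if Mann-Whitney, does not cure unequal variances, so the 5% level for equal means is not guaranteed when variances differ

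*Protocol article*

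**What the plan says.** Section {20a} of the protocol article (Statistical methods for primary and secondary outcomes) defines the primary endpoint as the "change in HDSS from baseline to day 40 in the ITT population" and applies a t-test "with a significance level of 5"%. The next sentence is the switch: "If assumptions of normality and homoscedasticity are unmet, a corresponding non-parametric test will be applied". It names no check, no threshold and no fallback test. It also leaves open whether one failed assumption is enough or both must fail.

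Section {14} (Sample size) sets the target of that test. It plans on "an assumed between-group difference in HDSS score of 1.8 points" with "a standard deviation (SD) of 1.7", "an alpha of 0.05, and a two-tailed" t-test, and "90% power to reject the null hypothesis (i.e., the averages of the two treatment groups are equal"). The planned hypothesis is thus about means, with one common SD for both arms.

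Sections {18a} and {20c} leave detailed methods and missing-data handling to a SAP that is to be final before database lock. Section {17a} keeps the statistical analysis blinded to allocation.

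**The concern.** Three features of the rule cause difficulty.

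1. **The test depends on the data.** Normality and equal variance of the HDSS change can be judged only from the outcome data, so the primary test is not known until those data are in.
2. **The remedy does not fit one of its triggers.** Unequal variance is a named reason to switch. The usual rank counterpart of the two-sample t-test, Mann-Whitney, has its nominal level for equal means only when the two distributions have the same shape. With unequal spread and skewness it can reject although the means are equal.
3. **The hypothesis changes.** The sample size addresses equal averages and a difference of 1.8 points. After the switch, the p-value no longer addresses that null.

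Unequal, skewed changes are plausible here. HDSS is bounded at 0 to 20 and entry requires a score of at least 5, so a patient who enters at 5 can improve by at most 5 points. Two disease presentations are also pooled. At stake is whether a significant primary result can be read as a difference in mean change at the stated 5% level.

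**Working it through.** **The plan's own figure.** With difference 1.8, SD 1.7, two-sided alpha 0.05 and 90% power, the standardised difference is 1.8 / 1.7 = 1.06. The exact noncentral t calculation gives 19.76, so 20 per arm. Allowing for "an expected drop-out rate of approximately 10"%: 20 / 0.9 = 22.2, so 23 per arm and 46 in total. The stated 50 is above this, on the safe side. With 50 × 0.9 = 45 evaluable patients the t-test has 93.5% power, and with 50 it has 95.6%. The gap between 46 and 50 does not bear on this point. What matters is that the calculation is for a test of means.

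**Why a rank test can reject when means are equal.** Take exponential changes, centred to mean 0, with SD s. The median is s × (ln 2 − 1) = −0.307 s. For s = 1.7 this is −0.52, and for s = 3.4 it is −1.04. The means are equal but the medians differ by 0.52 points, and a rank test responds to that difference.

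**Simulated error of the two-stage rule.** From the protocol: 25 per arm, SD 1.7, two-sided 5%. Assumed, because the protocol gives nothing:
- Shapiro-Wilk in each arm and a median-centred Levene test, each at 5%
- Mann-Whitney as the fallback
- the larger SD, the distribution shapes and the 25/20 split (smaller arm more variable)

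Means are equal in every scenario. Each has 30,000 simulated trials, so the Monte Carlo standard error near 5% is √(0.05 × 0.95 / 30,000) = 0.13 percentage points.

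| Scenario | t-test, no switch | Welch | Mann-Whitney | Switch if either fails | Switch if both fail |
|---|---|---|---|---|---|
| Normal, equal SD, 25/25 | 5.1% | 5.1% | 4.8% | 5.1% | 5.1% |
| Normal, SD 1.7 v 3.4, 25/25 | 5.2% | 4.9% | 5.3% | 5.2% | 5.3% |
| Normal, SD 1.7 v 3.4, 25/20 | 7.0% | 5.1% | 6.4% | 6.4% | 7.1% |
| Skewness 1, SD 1.7 v 3.4, 25/25 | 5.5% | 5.4% | 9.1% | 8.9% | 6.6% |
| Exponential, SD 1.7 v 3.4, 25/25 | 5.9% | 5.8% | 22.1% | 22.1% | 6.9% |

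A repeat with 4,000 trials per scenario gave about 8% to 9% (skewness 1) and 21% (exponential) when either failure triggers the switch, and 5% to 6% when both must fail.

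**Reading the table.** With unequal spread and skewness, the switch moves the analysis from a t-test with 5.5% to 5.9% error to a rank test with 9.1% to 22.1%. In the normal scenario with unequal arms, the excess is already present in the pooled t-test (7.0%), so it is not caused by the switch. In every row Welch lies between 4.9% and 5.8%.

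**Power.** At the planning values with 25 per arm, simulated power is 95.7% for Welch and 95.7% for the t-test. With SDs of 1.7 and 3.4 and the same 1.8-point difference, power is 62.9% for Welch and 60.0% for the two-stage rule if either failure triggers it.

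**The case against.** A reader might infer that the plan simply fails to keep its 5% level. The documents do not support that. If mesoglycan had no effect, so that both arms shared one distribution, the rule would keep about 5%. It also does so for normal data at an SD ratio of 2 with equal arms. The protocol gives one common SD of 1.7, so any SD ratio is an assumption. Read literally, the sentence requires both assumptions to fail, and the error is then about 6% to 7% even in the skewed scenarios. With ideal normal data the switch occurs in about 13% of trials on the either-fails reading and 0.4% on the both-fail reading, and the error stays near 5% on either.

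A reader might also infer an opportunistic choice of test. The documents do not show one: the analysis is blinded to allocation, and the rule refers to assumptions, not to p-values. Nor does a switch leave the reader without effect figures, since section {20a} promises means, medians and, where appropriate, 95% confidence intervals whichever test is used.

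Finally, the SAP may name the checks and the fallback test. That would settle the ambiguity. But a SAP that specified the checks would carry out the switch, not remove it, because the switch is fixed in the protocol. What also stands is that unequal variance is a stated trigger and that a rank test is no remedy for it under a null of equal averages.

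**Conclusion.** The point holds in a limited form, as a cheap improvement. The protocol lets the outcome data choose the primary test. If the fallback is Mann-Whitney, it does not answer one of the two problems that trigger it and no longer tests the planned null. The 5% level for equal means is therefore not guaranteed when variances differ, above all when the data are also skewed.

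The size depends on an ambiguity in the text. At an SD ratio of 2 with 25 per arm, the error is about 9% (skewness 1) to 21% or 22% (exponential) if either failure triggers the switch, and about 6% to 7% if both must fail. Welch gives 5% to 6% in the same settings. These figures rest on the assumed preliminary tests, fallback test, SD ratio and shapes. They show what the rule permits and do not predict this trial's error rate.

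**What to change.** Delete the switch and fix one primary test of the mean difference in HDSS change that tolerates unequal variance, whatever the data look like. A Welch t-test is sufficient. A linear model adjusted for baseline HDSS and the randomisation stratum, with heteroscedasticity-robust standard errors, would also do, but the adjustment goes beyond what this point requires. Report the estimated difference in points with its 95% confidence interval. Keep a rank test or a permutation test, stratified if wished, as a pre-specified sensitivity analysis that cannot replace the primary result.

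The cost is small. Welch has the same power as the t-test at the planning values, so the sample size stands. Some power is lost if the data are heavy-tailed. Because the rule stands in the protocol, a change in the SAP alone would leave the two documents in conflict. Both should be aligned before database lock, and this may need an amendment through the ethics committee under section {25}, in a trial that the article describes as already recruiting.

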### Interim analyses {21b}

There are no interim analyses planned.

### Methods for additional analyses (e.g., subgroup analyses) {20b}

There are no subgroup analyses planned. However, a sensitivity analysis may be added to the SAP according to the following subgroups: “patients with grade I, II or III HD” and “external thrombosed hemorrhoids”, if necessary.

### Methods in analysis to handle protocol non-adherence and any statistical methods to handle missing data {20c}

Statistical methods for substitution of missing values will be listed in the SAP, which will be finalized in Version 1.0 of the SAP, before the database lock.

### Plans to give access to the full protocol, participant-level data, and statistical code {31c}

Investigators will permit direct access to and review of all original trial documentation (signed informed consent forms, medical records, outpatient records) to the regulatory authorities, ethics committee, or the Sponsor with the provision that patient identities remain confidential.

Results of the trial will be documented by the trial Sponsor in an integrated clinical–statistical final report in accordance with GCP/International Council for Harmonization (ICH) guidelines.

## Oversight and monitoring

### Composition of the coordinating center and trial steering committee {5d}

The CRO is responsible for clinical monitoring activities as detailed in the monitoring plan drawn up in accordance with European Union GCP Guidelines.

### Composition of the data monitoring committee, its role and reporting structure {21a}

A data monitoring committee will not be utilized for this study. Instead, periodic monitoring visits will be conducted by the CRO. The CRO’s designee will review study data for accuracy, completeness, and consistency by comparing the data to that indicated on the source document during on-site monitoring visits and after transmission to the sponsor. Any discrepancies will be resolved by the investigator or designee as needed.

### Adverse event reporting and harms {22}

All AEs (serious and non-serious) which occur from signing the informed consent until 30 days after the last administration of the study drug will be recorded and described in the patient’s medical records and in the e-CRF. All events meeting the definition of serious will be reported as a SAE, regardless of whether or not they are identified during a protocol-specific assessment/visit. All SAEs must be reported by the Investigator to the Sponsor using the SAE form within 24 h of becoming aware of them; the initial report of a SAE may be reported by email.

Death is considered a SAE regardless of whether the event is expected or not, or considered associated with the study treatments. Any event requiring hospitalization (or prolongation of hospital stay) that occurs during a patient’s participation in a trial must be reported as a SAE, with the exception of hospitalizations for social reasons (in the absence of an AE) or pre-planned surgery/procedures. All SAEs must also be reported to the relevant ethics committee.

### Frequency and plans for auditing trial conduct {23}

Prior to initiating the trial, the trial Monitor will visit each center to clarify practical details of the trial (e.g., review of the protocol; procedures for obtaining informed consent, completion of the e-CRF and reporting of SAEs; management of the trial interventions [handling, storage, etc.] and trial documentation). During the trial, regular monitoring will be scheduled (2 × center visits and 4 × remote) by the trial Monitor to check the completeness and coherence of the data entered in the e-CRF, and compliance with trials procedures. In addition to these monitoring procedures, audits will be carried out by the Sponsor to ensure trial activities have been conducted and data recorded, analyzed, and reported in accordance with the protocol, GCP, standard operating procedures, and Italian regulatory requirements. Also, documents, facilities, and records related to the trial may be inspected by national/international regulatory authorities.

### Plans for communicating important protocol amendments to relevant parties (e.g., trial participants, ethical committees) {25}

Any protocol amendments will be submitted by the Sponsor to the ethics committee and approval documented prior to implementation. If the amendment substantially alters the design of the trial, each patient will be informed and their willingness to continue the trial will be confirmed in writing using an approved information sheet and consent form provided by the Sponsor.

### Dissemination plans {31a}

A copy of the final clinical trial report will be sent to relevant regulatory authorities (e.g., ethics committees), and the trial results may be published by the Sponsor, and/or presented at scientific conferences, after approval by the Scientific Coordinator.

## Discussion

The double-blind, randomized, controlled CHORMES trial is designed to investigate the efficacy and safety of mesoglycan versus placebo in patients with HD (Grade I–III or thrombosed external hemorrhoids). The effects of treatment on symptoms of HD and the impact on patient HRQoL will be evaluated. Analgesic use during treatment and pain will also be examined.

While an active comparator has not been included, the results derived from the study will allow clinicians to assess, albeit indirectly, the relative efficacy and safety of mesoglycan versus other available bioflavonoids for the treatment of acute HD. This includes, for example, a mixture of flavonoids investigated by Giannini and colleagues [31], and a micronized purified flavonoid fraction [33].

The key clinical endpoints of the current trial will be assessed using validated rating scales/scores (e.g., the HDSS [primary endpoint], the Short Health Scale_HD_, and the Vaizey score) in an attempt to make (indirect) comparisons versus trials of other flavonoid products for acute HD more relevant, although some authors have noted there remains a lack of standardized outcomes used in HD research [34], as well as interobserver variability in HD grading (as previously mentioned) [9].

A strength of the trial is its prospective, randomized, double-blind design, and it is the first study to evaluate the efficacy and safety of mesoglycan for acute HD in this standardized manner. It is the first standardized mesoglycan trial in patients with Grade I–III HD or external thrombosed hemorrhoids. As such, the trial results should provide good quality evidence to support its use in this patient population and will provide an update on the only placebo-controlled studies of mesoglycan, both of which were conducted over 35 years ago [27, 28]. Further, to the best of our knowledge, it is the first standardized mesoglycan trial in patients with Grade I–III HD or external thrombosed hemorrhoids to include a placebo control. As such, the trial results should provide good-quality evidence to support its use in this patient population and will provide an update to the existing literature. The two study centers from which patients will be recruited serve a high number of patients with HD across a wide range of HD severities, which implies that a good selection of patients will likely be enrolled into the study. However, the trial does have some limitations, in particular the relatively small anticipated sample size (*n* = 50), and that the use of concomitant medications such as analgesics and stool softeners will be allowed (although this will be recorded to allow for comparison between trial arms). Additionally, it is possible that patients with more severe disease are likely to be treated at the two study centers, so it is possible the patient population may be skewed towards patients with more serious pathology, although randomization procedures should reduce this risk*.*

## Trial status

The trial is currently operating under protocol Version 2.0, dated April 18, 2023. The first participant was recruited on 11 December 2023, and it is estimated that recruitment will be completed by October 2024 and the trial completed by December 2024.

## Data Availability

Data sharing is not applicable to this article as it reports the protocol of the CHORMES trial; however, once the trial is completed, the datasets used and/or analyzed during the study will be available from the corresponding author on reasonable request.

## Abbreviations

AE(s): Adverse event(s)
CHORMES: ACute HaemORrhoids treatment with MESoglycan trial
CRO: Contract Research Organisation
e-CRF: Electronic case report form
GAGs: Glycosaminoglycans
GCP: Good Clinical Practice
HD: Hemorrhoidal disease
HDSS: Hemorrhoidal Disease Symptom Score
HRQoL: Health-related quality of life
IHC: International Council for Harmonisation
IQR(s): Interquartile range(s)
ITT: Intention-to-treat
PP: Per protocol
SAE: Serious adverse event
SAP: Statistical analysis plan
SD: Standard deviation
Short Health Scale_HD_: Short Health Scale for Hemorrhoidal Disease
